**Discussion:**

Evidence of generalised iodine deficiency during pregnancy could lead to the promotion of interventions of prevention such as how to improve and intensify health care educational programmes for pregnant women.

**Trial Registration:**

ClinicalTrials.gov: NCT01301768

## Background

Iodine is a fundamental micronutrient for the organism which should be regularly administered through foods. Its function is essential for the synthesis of thyroid hormones which in turn act on the different organs and systems of the organism especially in the development of the central nervous system (CNS) from the earliest stages of embryonic and foetal development.

The ingestion of iodine depends on the type of foods consumed, their origin and preparation. Depending on the geographical area, products from the earth may have scarce iodine content. However, foods of marine origin are rich in this micronutrient [1]. In addition, it should be taken into account that foods lose iodine during their preparation: 20% is lost on frying, 23% on baking and 58% on boiling [2]. Some studies have shown that the iodine content of cows' milk differs according to what the animals are fed [3].

All these factors and alimentary habits make it difficult for the daily iodine requirements of the population to be covered through diet. Moreover, iodine is not stored in the body and must therefore be continually replenished. In normal conditions there is equilibrium between iodine intake and urinary elimination, and determination of iodine in urine (ioduria) constitutes a good indicator of iodine intake [4], with assessment of ioduria in a casual urine sample providing adequate information on the nutritional status of iodine [5].

During pregnancy there is an increase in thyroid hormone requirements due to the physiological modifications produced in response to the metabolic demands of pregnancy. This increase can only be achieved by a proportional increase in hormone production which directly depends on the availability of iodine in the diet. Moreover, gestation produces a physiological increase in the elimination of iodine in the urine because of a rise in glomerular filtration. In cases with an underlying deficit in iodine these modifications of pregnancy may not be compensated leading to failure of the mechanisms of adaptation. It is therefore very important to increase iodine intake from the beginning of gestation and even beforehand if possible, similar to the recommendations of supplementation of folic acid. The thyroid hormones available for embryonic and foetal tissue during the first trimester of gestation depend exclusively on maternal hormones and thus, a deficit in maternal iodine can have negative repercussions on prenatal development [6].

According to the World Health Organization (WHO) together with the United Nations International Children's Emergency Fund (UNICEF) and the International Council for Control of Iodine Deficiency Disorders (ICCIDD) the iodine needs of pregnant women have been established as 200 μg/L/day [4]. The ICCIDD has recently raised this recommendation to 250-300 μg/L/day. Maternal iodine intake may be calculated by the determination of ioduria (level of iodine in urine) taking into account that the factor of dilution in urine is greater in pregnant women than in the remaining population. The value of ioduria indicating optimum iodine intake during gestation should be between 150 and 230 μg/L [7]. Studies carried out in different European countries such as France, England, Germany, Switzerland, Ireland and Hungary have demonstrated the highly variable values of iodine deficiency (values less than 150 μg/L) in pregnant women, from 3.5% in England to 57.1% in Hungary [8-13].

Another aspect to consider within hygienic-dietetic habits of pregnant women is smoking and the repercussion this may have on maternal thyroid function. Smoking is considered a goitrogenic substance since it inhibits the absorption of iodine during both gestation and the period of lactation [14]. Smoking during gestation is associated with changes in the levels of thyroid function in both the mother and the foetus. The concentration of Thyroid-stimulating Hormone (TSH) in the mother (in the first and third trimester of gestation) and in the blood of the umbilical cord are lower and the T3 levels are higher which may trigger adverse effects for both [15,16]. It has also been reported that smoking during the period of lactation increases the risk of iodine deficiency which may lead to brain damage in the lactating child [14].

Iodine deficiency is not only a problem in developing countries but also affects most of the industrialised countries to a greater or lesser degree. It has currently been estimated that half of the population lives in areas in which there is a risk of having disorders due to iodine deficiency such as what occurs in several European countries such as Germany, Belgium, Denmark, Spain, France, Greece, Ireland and Italy. Zones with endemic goitre or some other alterations related to iodine deficiency have been detected in Spain [17-19].

Until several years ago the fundamental problem of iodine deficiency lay in endemic goitre but in the last decades studies have demonstrated a wide spectrum of disorders caused by iodine deficiency during pregnancy such as an increase in the number of abortions and dead foetuses, an increase in neonatal morbimortality and hearing defects in infants [20], a reduction in intellectual capacity and growth, congenital abnormalities with permanent neuromotor damage [21,22] as well as the attention deficit syndrome and hyperactivity [23,24]. According to the WHO, lack of iodine is the most frequent cause of mental retardation and irreversible brain lesions in the world [4].

Recent studies have demonstrated that iodine intake during gestation is low, even in areas where theoretically there are institutional prevention programmes to promote the consumption of iodised salt [18,25-27]. All these studies have been determining factors for the Spanish and the Catalan Societies of Endocrinology and Nutrition, the Spanish Society of Gynaecology and Obstetrics and the Ministry of Health and Social Policies to consider pregnant women as a risk group for disorders as a consequence of iodine deficit and to thereby recommend a diet rich in iodine and iodised supplements. Iodine deficiency in this population, albeit moderate, represents a high risk of cerebral lesions in the foetus [19,22].

The contribution of the quantity of iodine necessary for a good health status has been included as a basic human right: "All children have the right to an adequate intake of iodine to ensure normal development", especially children yet to be born and thus, "All mothers have the right to adequate iodine ingestion during gestation to ensure that their child achieves an optimum mental development" [28,29].

Some of the interventions most frequently studied during gestation have been the cessation of smoking and the promotion of maternal breastfeeding. McBride [30] hypothesised that pregnancy may be an "appropriate time for learning" to give up smoking since there is a greater perception of risk in this period and of personal results in pregnancy which provoke affective or strong emotional response and redefines social function or the self-conception of a woman, especially when failure in fulfilment of a social function results in social stigmatisation. This "appropriate time for learning" is not only appropriate for smoking cessation but also for any other health habit of the pregnant woman such as, for example, alimentary habits.

Some studies have demonstrated that the effectiveness of individual versus group Education for Health is similar [31-33] in different populational groups (diabetics, infant asthmatics or pregnant women), while others have reported favourable results in group interventions [34,35].

The interest in group education has grown in the last years, although very few studies have formally evaluated their effectiveness compared with individual education. In general, group versus individual education carries a reduction in health care costs in hospitalisations, medical consultations and the consumption of drugs for some chronic diseases such as diabetes mellitus and rheumatic diseases as well as different aspects of maternal-foetal health [36].

However, there are numerous difficulties involved in the development of group education such as for example the inadequate or imprecise definition of the educational objectives, the difficulties in evaluating the process and the results as well as the variable attendance of the patients and the limitations in the material and human resources available. Nonetheless, there is sufficient evidence to clearly indicate that these interventions are possible and effective.

The relevance of this study lays not only in knowing the type of educational intervention (group or individual), with modification of alimentary habits in pregnant women being the most effective, but also in performing a follow up of both hygienic-dietetic habits in the consumption of iodine rich foods and ioduria during the three trimesters of gestation. It is particularly of note that in the first trimester, the critical time in embryonic development, midwives in primary care centres should carry out a health care education intervention (individual or group) on these habits with special emphasis on the consumption of foods with high iodine content and iodine supplements.

If the results obtained by this study demonstrate the presence of generalised iodine deficiency during gestation, new studies would be required in other areas of Catalonia and the rest of Spain and would support the need to implement systematic programmes of iodine supplementation during gestation as well as the incorporation of specific educational programmes on alimentary habits.

## Hypothesis

The hygienic-dietetic habits of a pregnant woman has repercussion on both the nutritional status of the mother and the development and growth of the foetus. According to data obtained in a previous study carried out within the Primary Care setting of Catalonia, there is reduced consumption of foods rich in iodine since 71% report eating fish less than three times per week, 18% do not drink milk daily, only 42% use iodised salt for food condimentation and preparation and 18% of the pregnant women surveyed continue to smoke during gestation. We therefore consider that:

### 1st HYPOTHESIS

Most pregnant women in Catalonia have hygienic-dietetic habits which involve reduced intake of foods containing iodine (such as the eating of fish and the use of iodised salt for food condimentation) and in addition, an important percentage of these women continue to smoke during gestation.

### 2nd HYPOTHESIS

Most of the pregnant women in Catalonia have ioduria (levels of iodine in urine) with values of less than 150 μg/L (value considered as iodine deficiency) taking into account that the elimination of iodine in urine during gestation rises due to a physiological increase in glomerular filtration.

## Objectives

### General objective 1

o know the hygieninc-dietetic habits with respect to the consumption of iodine-rich foods and smoking of women during the three trimesters of gestation.

### General objective 2

To know the prevalence of ioduria less than 150 μg/L (iodine deficiency) and the factors associated with its appearance during the first three months of gestation.

### Secondary Objectives

1. Validate the questionnaire on nutritional iodine status in pregnant women.

2. Determine the iodine-rich foods consumed by pregnant women in each trimester of gestation and how these foods are prepared (boiled, fried, baked...).

3. Determine whether pregnant women use iodised salt in the preparation and condimentation of foods.

4. Determine whether pregnant women take any supplement containing iodine during gestation.

5. Describe the modifications in the smoking habits produced during gestation.

6. Compare the nutritional iodine status of the pregnant population between the different Primary Care Centres (PCC) participating in the study, ethnic groups, levels of education and gestational trimester.

7. Study the repercussions of the educational interventions on hygienic-dietetic habits and smoking as well as on iodurias and the taking of iodine supplements.

## Methods/Design

### Design

Cluster randomised, controlled, multicentre trial. Randomisation unit: primary care team (PCT).

### Setting

46 PCTs from the province of Barcelona that provide health coverage to urban, semirural and rural populations.

### Study population

All the pregnant women over the age of 17 years attending consultation to a midwife during the first trimester of gestation in the different participating PCC during the study period (2007-2010).

### Exclusion criteria

Pregnant women in the second or third trimester of gestation; pregnant women with diagnosed thyroid disease; pregnant women without a telephone; pregnant women with communication difficulties (cognitive or sensory deterioration, language barrier); pregnant women who do not consent to participate in the study.

### Sample size calculation

The sample size has been calcuated by multipying the size of a randomized simple design by the design effect. For the simple randomized design an alpha error of 0.05 and a beta error of 0.20 in a bilateral contrast are considered, requiring 204 pregnant women in the intervention group and 204 in the non intervention group to detect a difference greater than or equal to 15% in the prevalence of iodine deficiency between the two. After extensive review of the literature on group educational interventions in a pregnant population, the investigative team [37-40] considered that the intervention to be undertaken in the intervention group will achieve an improvement of at least 15% in hygienic-dietetic habits and thus in the levels of ioduria. A proportion of iodine deficiency of 44% in the non intervention group is assumed as indicated by studies performed in populations in the Pyrenees and the coast of the Maresme, areas near the study setting [18]. A loss to follow up of 15% has been estimated. Using an intracluster correlation coefficient of 0.05 [41-43], and based on an average of 25 pregnant women per PCT, the design effect is 2.2. Therefore, 898 pregnant women and 36 PCT are needed.

### Data Collection

*Dependent Variables*: iodine deficiency (yes, no), is defined as ioduria less than 150 μg/lL

Independent Variables:

Variables related to the woman (information obtained through a individualized interview):

- Administrative: PCT, midwife, data collection date, patient code, telephone number.

- Sociodemographic: date of birth, level of education, etnia.

- Obstetric: n° of pregnancies brought to term; n° premature births, n° of miscarriges and n° of live births, trimester of gestation of the woman (1st, 2nd or 3rd).

- Related to smoking: smoker (no, yes), cigarettes/day prior to gestation, cigarettes/day during gestation, ex-smoker because of pregnancy, ex-smoker and time since cessation of smoking.

- Related to consumption of iodine-rich foods:

▪ Consumption of milk: glasses/day

▪ Consumption of yoghourt: units/week and type (whole or skimmed).

▪ Consumption of cheese: rations/week and type (cured, semi-cured and fresh).

▪ Consumption of vegetables: times/week, usual preparation (raw, fried, grilled/baked, steamed, boiled) and use of water in which they have been boiled (yes, no and no answer).

▪ Consumption of vegetables and garden produce: times/week.

▪ Consumption of fish: times/week, usual preparation (raw, fried, grilled/baked, steamed, boiled).

▪ Consumption of tinned tuna: times/week.

▪ Consumption of tinned sardines: times/week.

▪ Consumption of meat and derivatives: times/week.

▪ Consumption of eggs: units/week.

▪ Consumption of fruit: units/week and types (strawberries, pineapple, peaches, bananas, oranges and others).

▪ Consumption of nuts: times/week.

- Consumption of iodised salt: yes (time of consumption), no.

- Consumption of multiple vitamins containing iodine: yes (type), no.

- Consumption of potassium iodine supplement: yes (type), no.

- Related to the intervention: study group (intervention, non intervention), attendance to group workshop (yes, no).

Variables related to the midwife (information obtained through a individualised interview): years in the profession, primary care nursing training, mean number of visits per day.

Variables related to the PCT (information obtained through an individualised interview): population assigned, mean age of population assigned, whether or not it is a teaching center for residents, number of midwives.

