**Methods/design:**

We will perform a cluster randomised, controlled, multicentre trial. Randomisation unit: Primary Care Team. Study population: 898 pregnant women over the age of 17 years attending consultation to a midwife during the first trimester of pregnancy in the participating primary care centres. Outcome measures: consumption of iodine-rich foods and iodine deficiency. Points of assessment: each trimester of the gestation. Intervention: group education during the first trimester of gestation on healthy hygiene-dietetic habits and the importance of an adequate iodine nutritional status. Statistical analysis: descriptive analysis of all variables will be performed as well as multilevel logistic regression. All analyses will be done carried out on an intention to treat basis and will be fitted for potential confounding factors and variables of clinical importance.

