### Statistical analysis

Data will be analysed in concordance with the Consort Cluster guide [44], and all analyses will be done on an intention to treat basis. A descriptive analysis and an analysis of baseline comparability between the study groups will be performed for the variables studied. A Student's t test or a Mann-Whitney U test will be used to compare means with two categories. An ANOVA test will be done to compare means with two or more categories, and a Chi- squared test or a Chi -squared tendency test will be done to compare categorical variables. A multilevel logistic regression will be carried out to evaluate the association between the dependent and the independent variables that were statistically significant in the bivariate analysis. All analyses will be adjusted for potential confounding factors and for variables with clinical relevance. All tests will be done with a 95% bilateral confidence interval. SPSS 15, STATA 10 and HLM6 will be used.

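### One covariate rule serves both the intervention effect and the associated-factors analysis, so workshop attendance and post-workshop habits can enter the model and attenuate the study-group effect

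*Protocol article*

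**What the plan says.** All references are to the protocol article.

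- **Data Collection** names one dependent variable, iodine deficiency (ioduria below 150 μg/L). Its single list of independent variables includes trimester of gestation, smoking, food consumption, iodised salt, iodine-containing vitamins, potassium iodine supplement and "Related to the intervention: study group (intervention, non intervention), attendance to group workshop (yes, no").
- **Statistical analysis** fits a multilevel logistic regression with the independent variables that were significant in bivariate analysis, and adds: "All analyses will be adjusted for potential confounding factors and for variables with clinical relevance". The same section commits to intention to treat.
- **Sample size calculation** bases the trial on a between-group difference in deficiency and expects that the intervention "will achieve an improvement of at least 15% in hygienic-dietetic habits and thus in the levels of ioduria".
- **Secondary Objectives**, item 7, treats habits, smoking and supplement taking, as well as ioduria, as things the educational intervention may change.
- **Description of the Study** puts the first interview and first urine request in Phase 4, the workshop (intervention group only) in Phase 5, and repeat interviews and ioduria in the second and third trimesters in Phase 6.

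**The concern.** A covariate measured after the workshop and changed by it is a mediator. Adjusting for it removes the part of the intervention effect that passes through it. The protocol's own account makes habits that route, and habits predict ioduria, so they are likely to pass a bivariate screen.

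Attendance raises a second problem. It can be positive only in the intervention group, so once it is in the model the study-group term no longer compares the groups as randomised.

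The same rule would also admit study group only if it passed the screen. At stake is the between-group difference on which the trial is sized: a workshop that works could show a reduced or absent group effect.

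**Working it through.** **1. Inputs (Sample size calculation).** Two-sided alpha 0.05 and power 0.80; 204 women per arm before the design effect is applied; a target worded as "to detect a difference greater than or equal to 15% in the prevalence of iodine deficiency between the two". Control-group deficiency is put at 44%. Also 15% loss, intracluster correlation 0.05 and 25 women per PCT.

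**2. Reproduce the plan's figure.** With p1 = 0.44, p2 = 0.29 and mean 0.365:

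- n0 = [1.960√(2 × 0.365 × 0.635) + 0.842√(0.44 × 0.56 + 0.29 × 0.71)]² / 0.15² = (1.3344 + 0.5660)² / 0.0225 = 160.5, so 161 per arm.
- With continuity correction: (n0/4)[1 + √(1 + 4/(0.15 n0))]² = 173.6, so 174.
- After 15% loss: 174/0.85 = 204.7, against 204 stated.
- Design effect: 1 + 24 × 0.05 = 2.2. Total: 408 × 2.2 = 897.6, so 898. Clusters: 897.6/25 = 35.9, so 36.

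The stated size reproduces. It is sized on the whole group difference, not on what remains after adjustment for habits.

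**3. Timing of the candidates.**

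| Candidate | When recorded | Relation to workshop |
|---|---|---|
| Cigarettes/day before gestation | refers to before pregnancy | before |
| Diet, salt, iodised vitamins, smoking at first contact | first trimester, Phase 4 | before |
| Habits interview repeated | second and third trimesters, Phase 6 | after |
| Workshop attendance | Phase 5 | part of the intervention |

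Trimester is itself on the list. Exclusion criteria bar women in the second or third trimester at entry, so trimester can vary only if follow-up records are analysed. The list therefore does not describe baseline data alone.

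**4. Power for the group coefficient by mediated share.** Effective women per arm: (898/2) × 0.85 / 2.2 = 173.5. Let m be the share of the 15-point effect that passes through the adjusted habits, and d = 0.15(1 − m) the remainder. Power (uncorrected test) = Φ{[d√n − 1.960√(2p̄(1 − p̄))] / √(p1(1 − p1) + p2(1 − p2))}, with p2 = 0.44 − d and p̄ the mean of p1 and p2.

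- m = 0: (0.15 × 13.171 − 1.3344)/0.6725 = 0.95, giving 83%.
- m = 0.5: (0.075 × 13.171 − 1.3593)/0.6915 = −0.54, giving 30%.

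| Assumed m | Remaining difference | Power |
|---|---|---|
| 0 | 15.0 points | 83% |
| 25% | 11.25 points | 58% |
| 50% | 7.5 points | 30% |
| 75% | 3.75 points | 10% |
| 100% | 0 | 5% (the alpha level) |

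**5. Check by simulation.** 400 trials per scenario, 36 clusters of 21 analysed women, latent intracluster correlation 0.05, cluster-robust logistic model, true difference about 14 to 15 points. Assumed: a perfectly measured habit score, benefit in attenders only, and attendance of 70% or 90%.

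| Model | Group OR | Power |
|---|---|---|
| Group only | about 0.54 | about 90% |
| Plus habits, m = 50% | 0.71 | about 39% |
| Plus habits, m = 75% | about 0.85 | about 14% |
| Plus habits, m = 100% | 0.99 | about 5% |
| Plus attendance, any m | about 1.0 | 4–7% |

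**6. Why attendance acts this way.** Every control has attendance = no, so the group term contrasts intervention-group non-attenders with controls. At 70% attendance that leaves 449 × 0.85 × 0.30 = 114.5 intervention women (effective 114.5/2.2 = 52.0); at 90%, 38.2 (effective 17.3). At 100%, group and attendance are collinear and the group effect cannot be estimated.

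**The case against.** The best defence is that Data Collection is an inventory, not a model. It also lists telephone number and patient code, and recording attendance is ordinary process data. The regression is described in terms of association, which suits General objective 2, where diet, salt, supplements and smoking are proper predictors. The article commits to intention to treat and to the CONSORT cluster guidance, and the Discussion says the design effect will be taken into account in all main analyses. An exact covariate set may be left to an analysis plan that is not shown.

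Much of this stands, and it rules out three stronger readings that a reader might infer:

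- *That everything listed is a consequence of the intervention.* It is not: first-contact values and smoking before pregnancy precede the workshop.
- *That the effect is certain to vanish.* The loss depends on which variables pass the screen and on a mediated share the protocol does not give. Phase 7 and the Discussion acknowledge that dietary iodine is hard to capture, and imperfectly measured habits would remove only part of a mediated effect.
- *That the abstract's "Outcome measures: consumption of iodine-rich foods and iodine deficiency" contradicts the use of food consumption as a predictor.* Habits can be an outcome under secondary objective 7 and a predictor under General objective 2.

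The defence does not remove the core point. The article does fix an entry rule, study group sits under it with attendance, and no other model for the group effect is given. A design-effect commitment deals with clustering, not with mediators, and the intention-to-treat commitment conflicts with a model that conditions on attendance.

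**Conclusion.** The point holds as a fault in the stated covariate rule. Where attendance or second- and third-trimester habits enter under it, the study-group coefficient no longer estimates the effect of being assigned to the intervention.

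For habits, the loss ranges from partial to complete. The power figures in the working assume that the stated share is additive on the risk-difference scale and is fully captured by the recorded habits; the simulation, on the logistic scale, shows the same pattern. For attendance, the near-complete loss assumes that only attenders benefit and that non-attenders are otherwise like controls. If non-attenders differ systematically, the coefficient is also open to selection bias.

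The documents do not show that the sponsor intends to report the fully adjusted coefficient as the effect. They show that it is the only clustered estimate specified.

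**What to change.** Replace the single rule with three stated analyses:

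1. **Intervention effect.** Post-workshop iodine deficiency in a multilevel logistic model with study group always included, a PCT random effect, and only prespecified pre-workshop covariates at individual and cluster level (for example first-trimester ioduria, age, education, ethnic group, obstetric history, baseline smoking, and midwife and PCT characteristics). Exclude attendance and all post-workshop diet, salt, supplement and smoking values. Apply no bivariate screen.
2. **Associated factors (General objective 2).** A separate model in which diet, salt, supplements and smoking may be predictors, with no intervention effect read from it.
3. **Secondary objective 7.** Post-workshop habits, smoking and supplement use analysed as outcomes by study group.

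Attendance can be kept for a separately labelled adherence analysis. The cost is analysis wording only; sample size and data collection stay the same.
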